### Study protocol

When trauma patients meet the inclusion criteria, a first blood sample is taken within 12 hours after trauma. This blood sample serves as a reference for the degree of inflammation immediately after injury. Because the first blood sample needs to be drawn within 12 hours after trauma, it is possible that the first sample is drawn without the necessary informed consent and will be analyzed directly. This delayed informed consent may be required because the inflammatory response after the initial trauma is visible in the blood within the first 12 hours after trauma. Of course, the informed consent is obtained as soon as possible if the patient or his/her legal representative is able to. If no consent is obtained, the analyzed blood and the data will be destroyed and the patients will not receive C1-INH or placebo, because the randomization will only take place after informed consent is obtained.

Patients receive femur fixation surgery according to the current protocol in the UMCU. Just after induction of anesthesia a second blood sample will be drawn and after this withdrawal the subject receives either C1-INH in a dose of 200 U/kg body weight (n = 35) or placebo (saline 0.9%, n = 35) intravenously. Two hours and six hours after the skin incision for the surgical procedure for femoral fixation the next blood samples are taken. The last samples are taken 24 and 48 hours and seven days after procedure of femoral fixation. An overview of the time frame of the study is shown in Figure 1.

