### Sample size calculation

The sample size calculation is based on damping of the increase in serum IL-6 concentration by 30% in the C1-INH group, compared to the placebo group [21,30,31]. With an expected standard deviation of 50% [30,31] and a relevant decrease of IL-6 concentration of 30% [21,30,31], 35 patients in each sample-group (C1-INH or placebo) are needed to find a statistically significant difference (power 80%, Type 1 error rate 0.05).

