### Statistical analysis

The primary endpoint, the Δ IL-6, will be determined with the use of a Students' *t-test*. The occurrence of inflammatory complications, such as MODS and ARDS, will be examined with the use of a survival analysis, such as Kaplan Meier or Cox proportional Hazard [32].

For comparisons, a *t-test *or Mann Whitney U-test will be used as appropriate.

Changes over time will be analyzed using repeated measurement analysis with time as within factor and treatment as between factor, using Analysis of Variance.

A *p*-value < 0.05 is considered statistically significant.

The data will be analyzed using software programs SPSS version 17.0 (SPSS Inc., Chicago, IL, USA) and GraphPad Prism (GraphPad Software Inc., La Jolla, CA, USA).

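### Repeated-measures ANOVA for changes over time keeps only patients with every included sample; a baseline-adjusted mixed model would use all of them

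*Protocol article*

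**What the plan says.** The Statistical analysis section assigns changes over time to a "repeated measurement analysis with time as within factor and treatment as between factor, using Analysis of Variance". It does not say which markers or samples enter, or whether the treatment main effect or the time-by-treatment interaction is the test of interest. The software is named: "The data will be analyzed using software programs SPSS version 17.0", together with GraphPad Prism.

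The Study protocol section sets out seven samples:

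- Two come before study drug: "a first blood sample is taken within 12 hours after trauma", and then "Just after induction of anesthesia a second blood sample will be drawn", with the infusion following. The second is the t = 0 sample.
- Five come after: "Two hours and six hours after the skin incision", and then "The last samples are taken 24 and 48 hours and seven days after procedure of femoral fixation".

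The primary endpoint is handled separately: "The primary endpoint, the Δ IL-6, will be determined with the use of a Students" t-test, comparing t = 0 with t = 6. The Objectives section lists mortality and length of hospital stay among the clinical outcomes.

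**The concern.** Classical repeated-measures ANOVA needs a full row per patient. A patient who lacks one of the entered samples contributes nothing, even if all the others were drawn. With sampling to day 7 after an injury of ISS 18 or more, late samples can be lost through death and through early discharge.

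Two things are at stake. The first is precision: observed values are thrown away in a trial of 70. The second is the comparison itself. The trial asks whether treatment affects mortality and length of stay. If it does, who still has a day-7 sample depends partly on treatment, and restricting to completers conditions on something that happens after randomisation.

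A smaller matter concerns the t = 0 sample. No treatment effect can exist there. Entered as a level of time, it is averaged into the treatment main effect; used as a covariate, it would sharpen the comparison instead.

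**Working it through.** **Figures in the plan.** None is given for this analysis. The inputs taken from the article are 70 patients (35 per arm) and the sampling schedule. The missing rates and correlations below are assumptions, shown as ranges.

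**1. Patients kept if only day 7 is missing.** This is the pattern that death or discharge would tend to produce. Kept = 70 × (1 − m). Each dropped patient may still have four post-infusion values (2, 6, 24 and 48 h). Observed post-infusion values in total = 70 × 4 + kept.

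| Day 7 missing (assumed) | Patients kept | Observed post-infusion values discarded |
|---|---|---|
| 10% | 63 | 7 × 4 = 28 of 343 (8%) |
| 20% | 56 | 14 × 4 = 56 of 336 (17%) |
| 30% | 49 | 21 × 4 = 84 of 329 (26%) |

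**2. Patients kept under scattered loss.** With 5% independent missingness at each of the six samples from t = 0, kept = 70 × 0.95^6 = 70 × 0.735 = 51.5, so about 51.

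**3. Dilution of the main effect.** Suppose the effect is zero at t = 0 and constant at δ over the five later samples. The average over six levels is (0 + 5δ)/6 = 5δ/6, a reduction of 1/6 (17%). The interaction tests whether the arm difference varies over time; t = 0 supplies its reference point, so this averaging does not apply to it.

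**4. What this does to power (illustrative).** Assumptions:

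- two-sided 5%
- equal correlation ρ between samples
- a constant effect of 30/50 = 0.6 SD at all five post-infusion samples

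The ratio 30/50 borrows the 30% difference ("a relevant decrease of IL-6 concentration of 30" per cent) and the 50% SD from the Sample size calculation, where they refer to IL-6 and not to every marker.

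The variance of a mean of k samples is (1 + (k − 1)ρ)/k. Adjusting the five-sample mean for t = 0 subtracts ρ². At ρ = 0.5:

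- six-sample mean: variance 0.583, standardised effect 0.5/√0.583 = 0.65
- five post-infusion samples: variance 0.600, effect 0.6/√0.600 = 0.77
- five samples adjusted for t = 0: variance 0.600 − 0.250 = 0.350, effect 0.6/√0.350 = 1.01

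Power comes from the noncentral t, and for the interaction from the noncentral F.

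| Test | ρ = 0.3 | ρ = 0.5 | ρ = 0.7 |
|---|---|---|---|
| Main effect, six samples, 35 per arm | 89% | 77% | 66% |
| Main effect, five post-infusion samples, 35 per arm | 96% | 89% | 81% |
| Post-infusion mean adjusted for t = 0, 35 per arm | 99% | 99% | over 99% |
| Interaction, six samples, 35 per arm | 53% | 69% | 91% |
| Main effect, six samples, 28 per arm (day 7 missing in 20%) | 81% | 67% | 56% |
| Interaction, six samples, 28 per arm (day 7 missing in 20%) | 42% | 58% | 83% |

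Losing 7 patients per arm to the full-row requirement costs about 8 to 12 percentage points, depending on ρ and on the test. A mixed model that keeps partly observed patients would stay near the adjusted row when few samples are missing.

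**The case against.** The strongest reply is that much of this depends on how the ANOVA is set up, and the article does not say. It names no time points, so inclusion of the later samples, and of t = 0, is inferred from the schedule. That stands, and it is why the point is conditional. If only samples that nearly everyone has were entered, the completer problem would be small.

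Several stronger readings are tempting but not supported:

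- **That all seven samples enter.** This would give a dilution of 2/7 and a loss of 30% of patients at 5% missingness per sample. The first sample is timed from the trauma and described as a reference for inflammation just after injury, whereas t = 0 is tied to the operation. Nothing says the first sample is a level of the time factor.
- **That the treatment effect is diluted in every test.** Only the main effect is. The interaction is the natural test of whether change differs by arm, and including t = 0 does not invalidate it.
- **That a quarter to a half of patients will be lost.** Losses of that size arise from independent missingness of 5% to 10% at every sample. Death and discharge act mainly on late samples, and the article gives no rate at all.
- **That the covariance assumption is an error.** The univariate test assumes sphericity, which is doubtful with spacing from hours to days. Greenhouse-Geisser or Huynh-Feldt corrections or the multivariate test deal with that, and the choice among them may be left to an analysis plan.
- **That the trial's main result is at risk.** The primary t-test uses t = 0 and t = 6 only, and the sample size does not rest on this ANOVA.

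Missing-data handling may also be described in a document not shown. The point does not rest on that silence: the stated method itself requires complete rows, and a plan that follows it inherits the requirement.

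**Conclusion.** The point holds in a limited form. The named method analyses completers only, and if samples to day 7 are entered, the loss can be both informative and costly. Under the assumed rates, 63 to 49 of 70 patients remain when day 7 alone is missing in 10% to 30%, or about 51 with 5% scattered loss over the six samples from t = 0. Entering t = 0 as a level of time shrinks the treatment main effect by a further 1/6.

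The true size cannot be established from the article, which gives neither a missing rate nor a correlation. The power figures rest on equal correlation and a constant 0.6 SD effect. The consequences are confined to the secondary time-course results. The change is worth making because the alternative is better under ordinary conditions and costs little.

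**What to change.** Replace the repeated-measures ANOVA with a linear mixed model for repeated measures:

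- **Outcome:** log concentration at the post-infusion samples (2, 6, 24 and 48 h, and day 7).
- **Fixed effects:** treatment, time, treatment-by-time and the log t = 0 value.
- **Covariance:** unstructured, with a simpler structure named in advance in case the model does not converge.
- **Patients:** all with at least one post-infusion sample.

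The cost is analysis wording only. The samples are the same, and the MIXED procedure in the SPSS version already named can fit the model. The Trial status section reports no patients included at the time of writing, so on that footing the change could precede any data.

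There is a small downside. The model assumes data are missing at random, which is a weaker assumption than a completer analysis needs but still an assumption. It does not by itself resolve truncation by death, because a marker value after death is not merely unobserved. This limit should be stated when the results are interpreted. The primary analysis needs no change on this account.

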### Interim analysis

In this study there will be two analyses performed, one interim and the final analysis, using the O'Brien Fleming method [33]. The alpha used for the interim analysis will be 0.0054, and for the final analysis the alpha used will be 0.0492.

The interim analysis will be conducted by an independent Data Safety Monitoring Board (DSMB) after the inclusion of 35 succeeding patients, The DSMB is composed of three independent members, of which two clinicians and one statistician. After the interim analysis the DSMB is able to make recommendations. In case of clear benefit, harm or futility of the treatment, the DSMB might decide to end the study early.

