### Study population

Seventy multi-trauma patients presented at the emergency department of the UMCU with an ISS ≥ 18 and a femur fracture which need fixation, will be included in the study. Patients are eligible for the study if they meet all the inclusion and none of the exclusion criteria (Table 1).

**Table 1 T1:** Patients in- and exclusion criteria

*Inclusion criteria*	*Exclusion criteria*
Multi-trauma patient ISS* ≥ 18 Femur fracture Age 18-80 years Informed consent	Congenital C1-inhibitor deficiency Use of immune suppressants Known hypersensitivity for blood Products Pregnancy Fixation of the femoral fracture with external fixation or osteosynthesis

*ISS = Injury Severity Score

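### The stated O'Brien-Fleming levels (0.0054 and 0.0492) slightly overspend the 0.05 error rate, and the general p < 0.05 line is not reconciled with them (wrong as written, minor)

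*Protocol article*

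**What the plan says.** Three places in the protocol article set an error level.

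- **Sample size calculation:** the design figures are given as "power 80%, Type 1 error rate 0.05". Whether the test is one- or two-sided is not stated here or elsewhere in the article.
- **Interim analysis:** there will be "two analyses performed, one interim and the final analysis, using the O'Brien Fleming method". The levels are given as "The alpha used for the interim analysis will be 0.0054, and for the final analysis the alpha used will be 0.0492". The interim takes place "after the inclusion of 35 succeeding patients", and the monitoring board may end the study early, including for clear benefit.
- **Statistical analysis:** the section begins with the primary test ("The primary endpoint, the Δ IL-6, will be determined with the use of a Students", that is, Student's t-test). After the survival, group-comparison and repeated-measures methods, it closes with the general rule that a p-value "< 0.05 is considered statistically significant".

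The total is fixed under Study population: "Seventy multi-trauma patients presented at the emergency department of the UMCU".

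**The concern.** A group-sequential pair of levels has one purpose: the chance of a false positive at either look, taken together, should equal the overall error rate. The article gives everything needed to check this: the method, the number of looks, the timing of the interim, the total sample size and the overall rate. The interim allows stopping for benefit, so it spends part of the error.

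Two questions follow. Does the printed pair add up to 0.05 at the planned timing? And which threshold decides the final primary test, 0.0492 or 0.05? This is the only decision rule for the only primary endpoint. If a p-value fell in the gap, choosing the threshold after seeing it would be hard to defend.

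**Working it through.** **Inputs.** Overall error 0.05 (Sample size calculation). Two looks, O'Brien-Fleming, levels 0.0054 and 0.0492, interim after 35 patients (Interim analysis). Total 70 (Study population). Information fraction t = 35/70 = 0.5.

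**1. What the printed pair is.** Read as two-sided levels, 0.0054 corresponds to z = 2.782 and 0.0492 to z = 1.967. The ratio is 2.782/1.967 = 1.414, which is √2. The classical two-look O'Brien-Fleming boundary with equal information steps has the form c√2 at the interim and c at the final, so the pair has the intended shape with c = 1.967.

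**2. Overall error of the printed pair.** Under the null hypothesis, Z1 and Z2 are standard normal with correlation √t = √0.5 = 0.707. The overall error is

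P(|Z1| > 2.782 or |Z2| > 1.967) = 0.0513.

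A simulation of two successive t-tests (35 patients, then 70; 4 million runs) gives 0.0516, with simulation standard error 0.0001. If the printed levels are read as one-sided, the overall error is 0.0509. The stated 0.05 is reproduced under neither reading.

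**3. The constant that would hold 0.05, two-sided.** Solving P(|Z1| > c√2 or |Z2| > c) = 0.05 gives c = 1.977. The boundaries are z = 2.797 and 1.977, which are levels 0.0052 and 0.0480. Other pairs that hold two-sided 0.05 at half information are:

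| Choice | Interim | Final |
|---|---|---|
| Classical O'Brien-Fleming | 0.0052 | 0.0480 |
| Keep the printed interim level | 0.0054 | 0.0479 |
| Keep the printed final level | 0.0026 | 0.0492 |
| O'Brien-Fleming-type spending, per side | 0.0031 | 0.0490 |
| O'Brien-Fleming-type spending, two-sided | 0.0056 | 0.0478 |

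The printed pair matches none of them.

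**4. One-sided 0.05.** Solving P(Z1 > c√2 or Z2 > c) = 0.05 gives c = 1.678. The boundaries are z = 2.373 and 1.678, which are levels of about 0.0088 and 0.0467.

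**5. Timing.** The printed pair, read two-sided, would come to 0.0500 only if the interim fell at about 70% of the information. The article places it at 50%.

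**6. The general 0.05 line.** With 0.0054 at the interim and 0.05 at the final, the two-sided overall error is 0.0521. The two sections give opposite answers only for a final p between 0.0492 and 0.05, a width of 0.05 − 0.0492 = 0.0008. For a final p between 0.0480 and 0.0492, both sections call the result positive although the correct two-sided boundary would not.

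**7. Power cost.** With the planned 30% difference, standard deviation 50% and 35 per arm, the standardised difference is 30/50 = 0.6. The expected final z is 0.6 × √(35/2) = 2.51. Two-sided group-sequential power is 0.709 with the printed pair and 0.705 with 0.0052/0.0480, a loss of 0.4 percentage points.

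**The case against.** The strongest reply concerns size. The excess is 0.0513 − 0.05 = 0.0013 on the two-sided reading and 0.0009 on the one-sided reading. The boundary shape is right. A result would be affected only if the final p fell between 0.0480 and 0.0492, or the interim p between 0.0052 and 0.0054. That stands, and it is why the point is minor.

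Second, the 0.05 line closes a list of methods for many outcomes, while the Interim analysis section is the specific rule for the sequential test. A reader can fairly let the specific rule govern, so this part is mainly a clarification. Still, the section with the 0.05 line also names the primary test, and neither section limits its own scope.

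Third, 0.0052/0.0480 cannot be called the only correct pair, because sidedness is never stated. The planned 35 per arm reproduces 80% power only with a one-sided 0.05 test; a two-sided test needs 44 or 45 per arm. This stands, and it makes the replacement conditional.

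Fourth, the article also allows stopping for futility, which would lower the error somewhat if always followed. No futility rule is given, so the printed levels cannot rely on it. The 0.0513 is therefore the figure with no futility stopping.

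The article cites a source for the method. The pair may have been taken from it, but that would explain its origin without making it hold 0.05 at this timing.

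**Conclusion.** The printed levels are wrong as written, but the error is minor. For a look at 35 of 70 patients they give an overall error of 0.0513 two-sided, or 0.0509 one-sided, against the stated 0.05. The unrestricted 0.05 line also differs from the 0.0492 set for the final primary test. The disagreement is confined to a final p between 0.0492 and 0.05, and following the 0.05 line at the final analysis would give 0.0521.

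A reader might infer more: that type I error control is seriously compromised, or that the two sections conflict over the whole range from 0.048 to 0.05. The documents support neither. The excess is about a tenth of a percentage point, and below 0.0492 the two sections agree with each other.

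The figures assume an interim at exactly half the information, approximately normal test statistics and no binding futility rule. The choice of replacement pair also depends on the sidedness of the test, which has to be stated first.

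**What to change.** 1. State whether the primary test is one- or two-sided, and at what overall level.
2. If two-sided at 0.05, replace the pair with 0.0052 (interim) and 0.0480 (final), or keep 0.0054 and set the final level at 0.0479. Alternatively, specify an O'Brien-Fleming-type spending function, which gives 0.0031 and 0.0490 at half information and adapts if the look does not fall at exactly 35 patients.
3. If one-sided at 0.05, recompute the pair; the levels are about 0.0088 and 0.0467.
4. In the Statistical analysis section, add that the primary endpoint is tested at the interim-adjusted level and that 0.05 applies to the other tests.

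The change is two numbers, a statement of sidedness and one sentence. It makes the final threshold slightly stricter and, on the two-sided reading, costs less than 0.5 percentage points of power. The Trial status section reports no patients included yet, so the change can be made before any data exist.

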## Discussion

This study represents a novel therapeutic approach for the attenuation of the inflammatory response in trauma patients undergoing surgical intervention. To our knowledge this is the first randomized, placebo-controlled trial examining the effect of the acute-phase protein C1-INH on the suppression of the dysfunctional inflammatory reaction in trauma patients during fixation of their femur fracture. Our research, focusing on the potential therapeutic effect of C1-INH, could have important impact on outcome of patients after a severe trauma.

C1-INH is proven to be effective as treatment for improving the outcome in a variety of inflammatory disease models [22,24], including SIRS induced by infusion of LPS [21].

The dosage C1-INH of 200 U/kg bodyweight is distinct from earlier clinical studies. It is shown that C1-INH synthesis increases up to 2.5 times the normal rate during an acute phase response [34,35]. Various states of severe inflammation, such as found during sepsis, burns and ARDS, give a rise in the consumption of C1-INH [36]. Nuijens and colleagues also showed a reduction in functional C1-INH in patients with sepsis complicated by shock or ARDS [37]. Caliezi et al claimed that this decrease in C1-INH levels, as result of the consumption, is probably due to a relative deficiency in functional C1-INH as result of enzymatic cleavage in inflamed or ischemic tissue [22].

We also expect consumption of C1-INH in the severely injured trauma patients in our study and thus a relative deficiency in functional C1-INH. We hypothesize that this consumption is mainly due to (i) the trauma itself, (ii) the blood loss during trauma, (iii) the possible extra blood loss during operation, and (iv) the dilution of the blood compartment during resuscitation because of the use of e.g. saline infusion or packed cells (erythrocytes). To compensate this natural consumption of C1-INH in our patients, we will administer a dose of 200 U/kg bodyweight, approximately a dose of 14.000-16.000 U per patient. This dose is expected to increase the circulating C1-INH concentration at least as found under acute phase conditions [21].

C1-INH is found to be well tolerated up to a dose of 19.000 units in patients suffering from acute myocardial infarction [38]. In the study of Strüber et al a dose of 15.000 U, followed by 7.500 U and 5.000 U (total of 27.500 U) was administered and tolerated without any side effects [39].

It is anticipated that this study will take three years to complete. The study is expected to start in October of 2011 and will end after the last blood sample is drawn from the seventieth successful included patient.

## Conclusion

To the best of our knowledge this study is the first randomized controlled trial designed to assess the use of C1-INH as a possible drug for attenuation of the inflammatory response in trauma patients after a second hit.

And, if our hypothesis is proved correct, it will result in increased functional outcome in trauma patients and reduced health care related costs.

